### Outcomes

The primary outcome for theme 1 (effectiveness) is the change in health-related quality of life (SF-36) at the individual level from baseline to follow-up at 12 months. This study hypothesizes that adding telehealthcare to usual care will lead to a significantly higher health-related quality of life for the included participants.

Secondary outcomes for theme 1 are changes in mortality and physiological parameters (diastolic blood pressure, systolic blood pressure, pulse, oxygen saturation, and weight) from baseline to the follow-up at 12 months. The clinical impact of telehealthcare is assessed as being beneficial if there is no changes in mortality and if pulse and blood pressure are lowered and oxygen saturation is raised.

The primary outcome for theme 2 is the incremental cost-effectiveness ratio (ICER) measured as the cost per quality adjusted life years (QALY) gained from baseline to follow-up at 12 months. It is expected that telehealthcare will increase the patients’ QALY compared with usual practice, since no difference in mortality and a higher health-related quality of life are expected. Furthermore, it is hoped that telehealthcare will reduce the number of admissions and readmissions to hospitals as well as the number of outpatient visits by 30%, which will reduce hospital costs [13,19]. However, these savings could be offset by other costs such as more visits to general practitioners, community care, medicine consumption or the cost of implementing telehealthcare.

Outcomes will be measured at both the individual level and at cluster level.

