### Statistical methods

Statistical analysis will be performed with an intention-to-treat principle and be presented according to the extensions of the CONSORT statement for cluster-randomized clinical trials [21]. Missing data (other than censoring) will be evaluated to assess the occurrence of specific missing data patterns and, if necessary, Multiple Imputation will be used and observations will be reported according to epidemiological guidelines [22]. If appropriate, an adjustment for differences in patient and/or cluster baseline characteristics (for example, age, gender, co-morbidities, educational level, marital status, proportion of COPD patients) in both the telehealthcare group and in the usual care group will be made.

To assess effectiveness in theme 1, a comparison of differences in mean SF-36 scores, mortality and physical measurements from baseline to 12 months after randomization between the telehealthcare group and the control group will be analyzed using statistical methods suitable for cluster-randomized trials, for example, multilevel modeling.

To assess the cost-effectiveness in theme 2, a point estimate of the ICER will be calculated after 12 months. The ICER is defined as the difference in arithmetic mean costs between the telehealthcare intervention and usual care divided by the difference in arithmetic mean effectiveness between the same intervention groups as shown in Equation (1).

Equation 1 shows how the incremental cost-effectiveness ratio (ICER) is calculated:

(1)$$\mathrm{ICER}=\frac{C_{\text{Telehealthcare}}-C_{\text{Usual}\;\text{care}}}{E_{\text{Telehealthcare}}-E_{\mathrm{Usual}\;\text{care}}}$$

The incremental effectiveness for the cost-effectiveness calculation is estimated from the utility scores from the EQ5D-3 L health-related quality of life questionnaire with Danish societal weights [23]. From these, QALYs can be calculated by linear interpolation of utility scores between baseline and the follow-up at 12 months by measuring the area under this curve.

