Three national registers are relevant in the present study: Firstly, *The Danish National Patient Register* contains national patient-level data for all hospital contacts (patient cpr-number, date of beginning/end of contact, diagnoses, treatments, and place of contacts). The register contains data on all inpatient, outpatient, and emergency ward visits in Denmark. Secondly, *The National Health Insurance Service Register* covers all contacts between patients and the primary care sector (general practitioners, physiotherapists, *etcetera*). The health authorities in Denmark use the register for administrative purposes, especially for the settling of accounts. The register contains data on all citizens, providers, and healthcare services reimbursed by the health authorities. Thirdly, *The Register of Medicinal Product Statistics* contains detailed information about the total sales of prescribed medicine in Denmark. Around 30 different items of information are registered every time a medicinal product is sold on prescription.

Finally, data on the use of community care is collected from the individual care systems in the residing municipalities and implementation cost are collected from cost diaries from the trial administration office.

Unit costs will be calculated for each of the resource parameters in order to determine the average costs per patient at baseline and at the 12-month follow-up. Point estimate for the average costs in the telehealthcare group and in the usual care group are then derived from univariate and multivariate analysis.

The cost-effectiveness analysis will be subject to both one-way and probabilistic sensitivity analysis (PSA). This is a standard way of analyzing and presenting results from a cost-effectiveness calculation that allows the recipients of the analysis to get a sense of the impact of different uncertainties in parameter values on the probability that telehealthcare is cost-effective at different levels of willingness to pay for an improvement in QALYs [26,27]. Another trial ambition is to expand the healthcare sector view to include costs incurred by patients and relatives (primarily due to transportation and time) and costs due to productivity loss to society that were excluded in in the base case scenario of total cost per QALY.

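### Theme 2 makes no firm commitment to adjust for baseline EQ-5D, which is half of its QALY measure, or to analyse costs and QALYs by the randomised districts

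*Protocol article*

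**What the plan says.** All places are in the protocol article.

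- **Outcomes:** "The primary outcome for theme 2 is the incremental cost-effectiveness ratio (ICER) measured as the cost per quality adjusted life years (QALY) gained".
- **Statistical methods, estimator:** "The ICER is defined as the difference in arithmetic mean costs between the telehealthcare intervention and usual care", divided by the corresponding difference in mean effectiveness (Equation 1). Effectiveness comes from EQ-5D utilities: "QALYs can be calculated by linear interpolation of utility scores between baseline and the follow-up at 12 months".
- **Statistical methods, costs:** "Point estimate for the average costs in the telehealthcare group and in the usual care group are then derived from univariate and multivariate analysis".
- **Statistical methods, uncertainty:** one-way and probabilistic sensitivity analyses are planned. The source of the input distributions is not stated.
- **Statistical methods, clustering:** SF-36, mortality and physical measurements "will be analyzed using statistical methods suitable for cluster-randomized trials, for example, multilevel modeling". That sentence is confined to theme 1, and costs and QALYs have no counterpart.
- **Statistical methods, adjustment:** ahead of both themes the article provides "If appropriate, an adjustment for differences in patient and/or cluster baseline characteristics". The examples are age, gender, co-morbidities, education, marital status and the share of COPD patients. Baseline utility and baseline cost are not among them.
- **Recruitment and Randomization:** the EQ-5D is completed before randomisation, and 26 districts in 13 matched pairs are then randomised.

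**The concern.** Theme 1 looks at change from baseline. Theme 2 looks at a level that contains the baseline value, so a baseline utility difference between arms enters the QALY difference unless it is adjusted for. With 26 randomised units, some difference is to be expected. The only adjustment provision is conditional and does not name the variable that matters most here.

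The same districts also generate the costs and the utilities. Study design describes them as self-contained with their own staff, and Usual practice says that community care varies between municipalities. Community care is a base-case cost, so clustering of costs is plausible. Nothing in the theme 2 text requires the probabilistic sensitivity analysis to reflect it.

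The stake is considerable: the Discussion ties possible adoption as a national standard to the solution proving cost-effective.

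**Working it through.** **1. The plan's own figure.** Sample size gives a difference of 5, SD 10, power 80%, two-sided 0.05, cluster size 50, size CV 0.5 and ICC 0.05.

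- Individual n per arm = 2 × (1.96 + 0.84)² × 10² / 5² ≈ 63.
- Design effect = 1 + ((1 + CV²) × m − 1) × ICC = 1 + (1.25 × 50 − 1) × 0.05 = 4.075.
- 63 × 4.075 = 256.7, and 256.7 / 50 = 5.13. That rounds up to 6 clusters, plus 1 as a small-sample allowance = 7 clusters, or 350 per arm.
- 700 / 0.9 = 778, consistent with the stated figure of around 800.

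The theme 1 calculation therefore reproduces with an unequal-cluster design effect. No precision figure is given for theme 2.

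**2. The same design effect applied to theme 2.** The Abstract expects 1,200 participants, so m = 1200 / 26 = 46.2. The plan's CV of 0.5 is kept. No ICC is given for utility or cost. The value 0.05 is the plan's SF-36 value, and the others are assumptions.

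| ICC | Design effect | SE ratio (square root) | Naive SE too small by | Coverage of a naive 95% interval |
|---|---|---|---|---|
| 0.01 | 1.57 | 1.25 | 20% | 88% |
| 0.02 | 2.13 | 1.46 | 32% | 82% |
| 0.05 | 3.83 | 1.96 | 49% | 68% |

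The shortfall is 1 − 1/√DEFF. Coverage is 2Φ(1.96/√DEFF) − 1.

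**3. Baseline utility in the QALY.** Linear interpolation over one year between two points gives QALY = (U0 + U12) / 2. Take a baseline difference d, no treatment effect, equal SDs at both times and correlation ρ. The expected 12-month difference is then ρd, and the QALY difference is d(1 + ρ) / 2.

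The chance SE of d with 600 per arm is SD × √(2 × DEFF / 600). SD and ρ are assumptions.

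- Low end (SD 0.20, ICC 0.01, ρ 0.5): SE = 0.20 × √(2 × 1.57 / 600) = 0.0145. Shift = 0.0145 × 0.75 = 0.011.
- High end (SD 0.25, ICC 0.05, ρ 0.7): SE = 0.25 × √(2 × 3.83 / 600) = 0.0283. Shift = 0.0283 × 0.85 = 0.024.

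For scale, a true 12-month utility gain of 0.03 (an illustration, since the article gives no expected gain) is worth 0.03 / 2 = 0.015 QALY under this interpolation. A one-SE imbalance would be about 0.7 to 1.6 times that amount (0.011 / 0.015 to 0.024 / 0.015).

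**4. Limits of the arithmetic.** The 13 matched pairs are ignored, and pairing could lower these figures. All 1,200 participants are used, before loss to follow-up. Steps 2 and 3 overlap: a cluster-aware SE for the unadjusted QALY difference already contains the variance from chance imbalance, so the two effects should not be added together.

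**The case against.** A reader might infer that theme 2 uses raw arm means, allows nothing for baseline, and understates its uncertainty. The text does not support any of these.

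- An arithmetic mean names the quantity to be estimated. Equation 1 can be met by regression-adjusted means, and costs "are then derived from univariate and multivariate analysis".
- The general adjustment provision precedes both themes, and its list is illustrative, so baseline utility is not excluded.
- No sentence says that the probabilistic analysis ignores districts, and the section commits to reporting under the CONSORT extension for cluster trials. The coverage of 68% to 88% belongs to a naive interval that the plan nowhere proposes.
- Chance imbalance is not bias under randomisation.
- The utility SD, the correlation and the ICC for utility and cost are all outside the article.
- Model form and covariates often sit in an analysis plan, which is not shown and may already settle this.

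These points stand, and they limit the finding to a missing commitment rather than a demonstrated error. They do not remove it. The article fixes a QALY definition with baseline utility inside it, leaves adjustment conditional, and makes the cluster commitment for one primary theme but not the other. Multivariate analysis of costs deals by itself with neither clustering nor the QALY side.

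**Conclusion.** The point holds as a gap in commitment. Baseline utility is half of the theme 2 effect measure, adjustment for it is neither named nor firm, and a cluster-respecting analysis is committed to for theme 1 only.

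The consequence is conditional. It arises only if the ratio and its sensitivity analysis are run on unadjusted means without regard to districts, which the text leaves open. In that case a one-SE imbalance moves the QALY difference by about 0.011 to 0.024, and a naive SE is about 20% to 49% too small. The lower end rests on an assumed ICC of 0.01. The upper end extrapolates the SF-36 ICC, which the plan itself calls conservative, to utility and cost.

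It would be wrong to conclude that the estimator is biased. The harm is extra variance in the single ratio that decision-makers will see. This is an inexpensive improvement worth settling before analysis, given that the ratio is a primary outcome.

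**What to change.** State in advance, in the analysis plan or health-economics plan, if it is not already there:

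1. Incremental cost and incremental QALY are estimated with a method that respects the randomised districts and pairs, for example a bivariate multilevel model or a cluster bootstrap.
2. Baseline EQ-5D is a fixed covariate in the QALY equation, and baseline cost is one in the cost equation.
3. The ratio, the probabilistic sensitivity analysis and the acceptability curve are drawn from those estimates and their covariance.
4. The unadjusted Equation 1 result is reported as descriptive.

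The cost is wording and some analysis code. No new data collection is needed: the EQ-5D is collected before randomisation, and Statistical methods already plans average costs per patient at baseline.

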### Ethics

The study is conducted in accordance with the Helsinki Declaration. The trial has been presented to the Regional Ethical Committee for Medical Research in the North Denmark Region where it was determined that no ethical approval was necessary. The trial has also been authorized by the Danish Data Protection Agency.

## Discussion

There has been a call for large-scale clinical trials with rigorous cost-effectiveness assessments in telehealthcare research. This study is meant to improve the international evidence base for the effectiveness and cost-effectiveness of telehealthcare to patients suffering from COPD by implementing a large-scale pragmatic cluster-randomized clinical trial throughout the geographical area of North Denmark Region. Changes in health-related quality of life and costs are evaluated using a broader range of cost categories than most existing studies.

For practical and ethical reasons, the involved stakeholders decided that all eligible patients and municipality districts in North Denmark Region should be able to option for the telehealthcare intervention no later than 12 months after randomization. It could be argued that the 12 month timeframe of the trial may be too short to capture all future costs and outcomes since COPD is a chronic disease. On the other hand, there is to our knowledge no evidence to suggest an appropriate timeframe for including all relevant future costs and clinical outcomes. However, a modelling study extrapolating QALY differences over a longer period could be considered to supplement the economic evaluation performed in this clinical trial.

The expectation is that the results of the trial can be generalized to all municipalities in Denmark. ‘The National Danish Action Plan for Dissemination of Telemedicine’ has determined that if the telehealthcare solution in this trial proves cost-effective, it can serve as a national Danish standard for a technological platform as well as an implementation model for telehealthcare to this patient group. The technical platform is therefore not patented, and codes and documentation of how the study was implemented will be published.

## Trial status

Recruitment is ongoing.

## Abbreviations

COPD: chronic obstructive pulmonary disease; ICER: incremental cost-effectiveness ratio; QALY: quality adjusted life years
